### Strategies to Improve Adherence to Interventions

To improve compliance, the content and importance of the protocol and the meaning of participating in the study will be explained to improve participant understanding. Furthermore, to reduce participant burden, such as by minimizing the frequency of visits, day 31 will have an option for telephone confirmation. To monitor compliance, the participants will be asked to maintain a medication diary, which will be checked regularly.

### Relevant Concomitant Care Permitted or Prohibited During the Trial

During the study period, adjustments to the administered medications or the initiation of new medications will be permitted. However, to prevent evaluation of efficacy, the use of herbal medicines with the same efficacy as orengedokuto will be prohibited. For patients at high risk of thromboembolism, antithrombotic drug (anticoagulants and antiplatelet drugs) administration should be continued where discontinuation would otherwise increase the risk of thromboembolism. Such patients include those within 2 months of coronary stent placement, those within 2 months of cerebral revascularization, those with a history of cardioembolic stroke, or those with atrial fibrillation complicated by valvular heart disease. For cases in the low-risk group for thromboembolism in which the discontinuation of antithrombotic drugs is possible, discontinuation will be considered. Once the bloody stool has stopped, antithrombotic therapy should be promptly resumed.

### Provisions for Posttrial Care

Participants will be managed by a physician according to routine care practices, including the management of any complications. The treatment protocol in this study will be covered by health insurance and will not be considered a medical procedure beyond regular medical care. Any health-related harm caused by participating in this study will be treated as appropriate according to the patient’s condition as part of regular medical care and will be covered by health insurance.

### Outcomes

#### Primary End Point

The primary end point of this study is the proportion of patients who experience rebleeding. Rebleeding is defined as the occurrence of new-onset significant hematochezia within 30 days of study enrollment (including the day of enrollment). Significant hematochezia is characterized by either a drop of 2 g/dL or more in hemoglobin level or visible gross blood that obscures the bottom of the toilet bowl. The evaluation of the outcome will be conducted by blinded investigators.

#### Secondary End Points

The secondary end points of this study are the duration of hospitalization, the number of days until the initiation of oral intake, the severity of rebleeding (including the timing and degree of anemia), and the proportion of patients experiencing recurrent rebleeding.

Safety assessments will involve evaluating each observed adverse event for its causal relationship with the investigational treatment, and the frequency of each event will be recorded accordingly.

Observational and laboratory assessment items will include detailed patient background and clinical data. These will consist of the patient identification code, the date and time of hematochezia onset, admission and discharge dates, sex, age, blood type, smoking and alcohol consumption status, history of hematochezia, history of CDB, presence of comorbidities, Charlson Comorbidity Index [24], use of nonsteroidal anti-inflammatory drugs within the past 2 weeks, concomitant medications at the time of registration, presence or absence of contrast-enhanced computed tomography, extravasation findings, and the bleeding site if present.

Other parameters to be recorded include anthropometric measurements (height and weight), general condition, vital signs, colonoscopic findings, whether bowel preparation was performed using oral lavage or enema, blood test results, medication adherence, confirmation of hematochezia, and documentation of adverse events.

### Sample Size

The target sample size was determined based on a retrospective analysis conducted at 5 participating institutions. This analysis reviewed the number of cases of CDB and the rate of rebleeding within 30 days over a 1-year period (January-December 2019; UMIN000049020). Among the patients who did not undergo endoscopic hemostasis for CDB, the 30-day rebleeding rate was 1 of 11 (9.1%) patients who received orengedokuto, compared with 15 of 48 (31.3%) patients who received only conservative treatment (*P*=.23).

The sample size was calculated based on the primary end point: the proportion of patients with rebleeding. Assuming a rebleeding rate of 31.3% in the placebo group (standard treatment only) and 9.1% in the orengedokuto treatment group, the minimum number of patients required to achieve a 2-sided significance level of 5% and a power of at least 80% was estimated. Using the Fisher exact test for a 2-sample comparison of proportions, with the PROC POWER procedure in the statistical analysis system, the required sample size was calculated to be 57 patients per group. Considering potential dropouts and ineligible cases, the planned total enrollment is set at 120 patients.

### Recruitment

At least 6 facilities will be included to ensure a sufficient sample size. Fifty-nine patients with CDB underwent conservative treatment at the 5 facilities over the course of a year; hence, we believe that by increasing the number of facilities to 6, it will be possible to achieve adequate case registration. Monthly newsletters, including recruitment rates and targets, will be provided to the investigators.

### Assignment of Interventions

#### Blinding

Prior to allocation, the person responsible for investigational drug allocation shall verify the indistinguishability of the investigational drug and placebo from each lot in terms of appearance, shape, and labeling of each treatment group.

After confirming the indistinguishability of the investigational drugs at the investigational drug storage facility, the person responsible for investigational drug allocation will assign investigational numbers to the drugs (active and placebo) in accordance with a key code table created in advance using a random number table.

The investigational drugs, labeled with drug numbers, will then be transported in fixed quantities from the storage facility to the clinical trial sites.

At the trial site, the PI (or subinvestigator) or study collaborator will log into the minimization web system provided by Medical Research Support Co, Ltd, register the study participant, and enter the allocation adjustment factors. The system will then assign the appropriate investigational drug number to each participant.

Specifications for the minimization web system are described in the allocation procedure manual and will be managed by the person responsible for drug allocation.

#### Procedure for Unblinding

In cases such as a participant’s request or the occurrence of adverse events, the investigational drug allocation manager may unblind (open the key code) and reveal the allocated intervention under the instructions of the PI and the chairperson of the Efficacy and Safety Evaluation Committee.

##### Storage of the Key Code

The key code table will be stored by the person responsible for investigational drug allocation.

##### Opening of the Key Code

The key code will be opened as follows:

In principle, the key code will be opened by the person responsible for drug allocation only after all drug administration is complete and the contents of the case report forms (CRFs) have been finalized.The statistician will perform statistical analyses based on the key code received from the drug allocation manager.

### Investigational Drug and Placebo Management

The procedures listed below will be followed to ensure proper management and accountability of the investigational products throughout the study:

The receipt and return of investigational drugs will be recorded in the drug accountability record.The PI or their designee will record the date of receipt and the lot number of the investigational drugs in the drug management log.The investigational drugs will be stored under the recommended storage conditions (room temperature) in a secure location with restricted access.During the clinical study, the following information will be recorded in the drug accountability log:Patient identification code to whom the drug was dispensed; andDate of dispensing, quantity dispensed, date of return, and quantity returned.The drug management log will be readily available at all times for monitoring, review by the ethics committee, and inspection by other relevant regulatory authorities.The drug management logs and storage locations of investigational drugs will be reviewed during monitoring.Unused investigational drugs will be returned to the PI or designee as soon as they are deemed unnecessary. At the end of the study, all unused investigational drugs remaining at the trial site will be properly disposed. The monitor will confirm that disposal has been performed.

### Data Collection and Management

The PI or subinvestigator at each participating medical institution will promptly complete a CRF after collecting the specified tests and evaluation items. In this study, paper-based CRFs will be sent to the data center via fax. Data will be entered directly into a database managed by the data center.

Participants who do not attend their scheduled visits will be contacted by phone. Follow-up will be continued regardless of protocol adherence.

The PI will appoint a data management supervisor to oversee and coordinate the timely creation of CRFs and data collection to ensure the development of an appropriate dataset. The data management supervisor will be responsible for monitoring the progress of CRF completion and data entry, as well as for conducting data review and cleaning. Furthermore, the data management supervisor will be accountable for the quality of the datasets used in the analysis.

The PI will also appoint a monitoring officer to conduct central monitoring to ensure that the study is being conducted safely and in accordance with the study protocol, the Clinical Research Act, and other applicable regulations and that the data are being accurately collected. The monitoring officer will report the results to the PI.

Personal information in the database will be password-protected on a secure network. No identifying information will be used in any analysis, report, or publication. Biological specimens for genetic or molecular analysis will not be collected in this study.

### Statistical Methods

The full analysis set (FAS) will include all enrolled participants, excluding those who are found to be ineligible, those who do not receive any study treatment after enrollment, and those for whom no postenrollment measurements are available. The per-protocol set will include participants in the FAS, excluding those for whom the primary outcome is not evaluable and those with major protocol deviations, such as incorrect treatment allocation, use of prohibited concomitant treatments, or treatment adherence of 70% or less. The safety analysis set will include all enrolled participants who receive at least one dose of the study treatment.

For the primary end point, the FAS will be used as the analysis population. The proportion of patients with rebleeding will be calculated for each group, and intergroup comparisons will be performed using Fisher exact test, consistent with the method used for sample size calculation. A 2-sided significance level of 5% will be applied. Additionally, a sensitivity analysis will be conducted using the per-protocol set to assess the robustness of the results.

For the secondary end points, the FAS will also be used as the analysis population. Statistical comparisons will be performed between the 2 groups for the following variables:

Mean duration of hospitalization;Mean number of days until the initiation of oral intake;Severity of rebleeding (including timing and degree of anemia); andProportion of patients with recurrent rebleeding (re-rebleeding)

The Wilcoxon rank-sum test will be used to analyze continuous variables. Fisher exact test will be used to analyze categorical variables. No adjustment for multiplicity will be made for the secondary end point analyses, which will be considered exploratory. Further details will be prespecified in the statistical analysis plan, which will be finalized before database lock and unblinding.

The safety analysis set will be used for the safety analysis. Safety will be evaluated separately for the treatment and follow-up periods. Adverse events will be assessed in terms of type, frequency, severity, and causal relationship with the investigational drug. The incidence rates of adverse events will be calculated and compared between groups. If statistical testing is applied, the Fisher exact test will be used for comparison.

No interim analyses are planned. Missing data will not be imputed and will be treated as missing in the analysis. If missing data are expected to affect outcomes, sensitivity analyses will be planned and conducted accordingly. All sensitivity analyses will be prespecified prior to database lock.

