### Interventions

Both groups will receive standard treatment (bowel rest through fasting and intravenous fluid administration), which is the standard treatment for CDB. When comparing the orengedokuto group with the placebo group, the only difference between the test groups will be the presence or absence of the active ingredient in the intervention being tested. There is no available treatment for CDB; hence, there is no inherent disadvantage of using a placebo. Moreover, the placebo effect can be controlled by using a placebo as the test drug for the placebo group.

The intervention will commence within 24 hours of registration. Based on the allocation results, patients will receive either orengedokuto (orengedokuto plus standard treatment) or placebo (placebo plus standard treatment) for 14 days. Patient registration will be conducted through a web-based registration and allocation system managed by the data center. An interactive web system will ensure that the allocation remains concealed until it is assigned. The allocation sequence will be computer-generated and allocated using the interactive web system. Investigators or subinvestigators at each participating site will access the registration system via its URL to complete registration and obtain allocation results.

Subsequently, an observational follow-up will be conducted for 31 days from the start of treatment. Standard care refers to fasting and bowel rest, which are routinely used to treat CDB.

Orengedokuto is a traditional herbal medicine used in Japan. Each dose (6 capsules) contains the following herbal ingredients: ogon (3.0 g), oren (1.5 g), sanshishi (2.0 g), and obaku (1.5 g). Regarding the dosage, in accordance with insurance coverage guidelines, the recommended regimen is 2 capsules 3 times daily. Therefore, patients will take 2 capsules of either orengedokuto or placebo 3 times a day. As our retrospective analysis found that cases of rebleeding occurred within 10 days, we have set the treatment duration to 14 days. This study is being conducted using the investigational drug, orengedokuto, and a placebo both provided free of charge by Kotaro Kampo Pharmaceutical Co, Ltd. The placebo contains corn starch as the inactive filling material and was manufactured and supplied by Kotaro Kampo Pharmaceutical Co, Ltd. The placebo capsules were designed to be indistinguishable from the active capsules in appearance, shape, labeling, packaging, and administration schedule.

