### Criteria for Discontinuing or Modifying Allocated Interventions

The PI or subinvestigator shall discontinue the investigational drug and terminate the patient’s participation in the study if it is determined, for any of the following reasons, that continued participation is not feasible. In such cases, the reason for discontinuation will be explained to the study participants, as necessary. Furthermore, the postdiscontinuation treatment will be handled sincerely to avoid any disadvantages to the participant.

Discontinuation criteria are as follows:

If the participant withdraws consent to participate in the study;If it is found after enrollment that the participant does not meet the eligibility criteria (inclusion/exclusion criteria);If the underlying disease worsens and continued administration of the investigational drug is deemed inappropriate;If complications worsen and make it difficult to continue the study;If it becomes difficult to continue the study owing to adverse events;If the participant is found to be pregnant;If the participant exhibits extremely poor adherence, such that medication compliance is objectively deemed to be below 70%;If the underlying disease is completely cured and continued administration is no longer necessary;If the entire study is discontinued; andIf the investigator otherwise deems it appropriate to discontinue the participant’s involvement in the study for any other reason.

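### The per-protocol adherence rule can, as written, exclude a patient because of the primary event, which weakens the only named sensitivity analysis

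*Protocol article*

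**What the plan says.** All references are to the protocol article.

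- **Primary analysis (Statistical Methods).** "For the primary end point, the FAS will be used as the analysis population". The full analysis set has no adherence exclusion.
- **Per-protocol set (same section).** It is the full analysis set less patients whose primary outcome cannot be evaluated and those with major protocol deviations. The examples of deviations include "use of prohibited concomitant treatments, or treatment adherence of 70% or less". No exception is given for patients who stop drug after a rebleed, and the denominator of adherence is not defined.
- **Its role (same section).** "a sensitivity analysis will be conducted using the per-protocol set to assess the robustness of the results". No other sensitivity analysis is named. The article allows further ones if missing data are expected to affect outcomes.
- **Regimen (Interventions).** Treatment lasts 14 days, and "patients will take 2 capsules of either orengedokuto or placebo 3 times a day".
- **Timing of events (Interventions).** "As our retrospective analysis found that cases of rebleeding occurred within 10 days, we have set the treatment duration to 14 days".
- **Stopping drug (Criteria for Discontinuing or Modifying Allocated Interventions).** One criterion reads: "If the underlying disease worsens and continued administration of the investigational drug is deemed inappropriate". Rebleeding is not itself listed.

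**The concern.** Adherence is observed after randomization, and the primary event can influence it. A patient who rebleeds early and then stops drug has low adherence as a consequence of the outcome. If that patient is dropped for low adherence, the event goes too. With a working drug there are more events in the placebo arm, so more would be lost there and the contrast would shrink on the risk-difference scale.

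The 70% cut makes this a practical matter. On a 14-day denominator it falls at almost the same point as the 10-day window in which the retrospective rebleeds occurred. What is at stake is the reading of the robustness check: a sound primary result could be followed by a weaker per-protocol result whose weakness comes from how the set was built.

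**Working it through.** **1. The plan's own figure.** Inputs from Sample Size: 31.3% versus 9.1%, two-sided 5%, power at least 80%, Fisher exact test. Full binomial enumeration gives power of 79.3% at 56 per group and 80.3% at 57. The stated 57 per group reproduces.

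**2. Where the 70% cut falls, if the denominator is the whole course.**

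- Scheduled capsules: 2 × 3 × 14 = 84.
- Threshold: 0.70 × 84 = 58.8 capsules, and 58.8/6 = 9.8 days.
- Nine full days: 54/84 = 64.3%, excluded.
- Ten full days: 60/84 = 71.4%, kept.

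A patient who takes every capsule and stops by the end of day 9 therefore meets the exclusion. The article does not state the day from which the retrospective 10 days were counted, so the match with the cut is approximate.

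**3. The same patient, if the denominator is capsules due up to stopping.** Adherence is 54/54 = 100%, and the patient stays in the set. The result depends entirely on a definition that the article does not give.

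**4. Illustration of size.** Let f be the share of events followed by stopping early enough to be excluded. The documents do not give f. It is assumed equal in both arms, and no patient without an event is removed. An arm with event rate p then has:

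- per-protocol rate = p(1 − f)/(1 − pf)
- arm size = 57(1 − pf)

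Example at f = 50%: placebo 0.1565/0.8435 = 18.6%; orengedokuto 0.0455/0.9545 = 4.8%; difference 13.8 points. Power is for the two-sided Fisher test at the reduced arm sizes, rounded to whole patients.

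| f (assumed) | Expected events, placebo / active | Rates | Risk difference (points) | Risk ratio | Power |
|---|---|---|---|---|---|
| 0 | 17.8 / 5.2 | 31.3% vs 9.1% | 22.2 | 0.29 | 80% |
| 25% | 13.4 / 3.9 | 25.5% vs 7.0% | 18.5 | 0.27 | 73% |
| 50% | 8.9 / 2.6 | 18.6% vs 4.8% | 13.8 | 0.26 | 56% |
| 75% | 4.5 / 1.3 | 10.2% vs 2.4% | 7.8 | 0.24 | 31% |

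**5. Relative measures.** The odds in each arm become p(1 − f)/(1 − p), so the factor (1 − f) cancels. The odds ratio stays at (0.091/0.909)/(0.313/0.687) = 0.22 for every f below 1. Under this model the loss is in events, precision and the absolute difference; the relative effect is hardly distorted.

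**The case against.** The strongest reply is that the documents do not establish the mechanism.

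- **Denominator.** The discontinuation criteria use compliance below 70% as a reason to stop during treatment. On a 14-day denominator every fully compliant patient would be below 70% through day 9, so that rule makes sense only for doses due so far. If the per-protocol rule uses the same measure, a patient who was compliant until a rebleed is kept. This stands as a plausible reading, but the article does not state it.
- **Stopping after a rebleed.** No section says that a rebleed stops drug. The criterion needs both worsening and a judgement about continuing, and patients who rebleed and continue are kept. A stop directed by the protocol might also not be counted as a deviation. Both points stand.
- **Other early stops.** Patients without a rebleed may stop early too, for adverse events or because the disease is judged cured. The set need not lose events only.
- **Left to the analysis plan.** The derivation of adherence is commonly specified there, and the article defers detail to a plan finalized before database lock and unblinding. An undefined denominator alone would be no finding. However, the article itself fixes the threshold, the exclusion and the role of the set. Its missing-data clause does not clearly reach these patients, because a patient who has rebled has an observed outcome.

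A reader might infer that the rule is bound to strip out primary events, or that the trial's main result is biased. The documents support neither. The first needs two unstated conditions, and the second is ruled out because the primary analysis set has no adherence exclusion.

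**Conclusion.** The concern holds as a conditional risk. The per-protocol rule permits exclusion caused by the primary event, and nothing in the article prevents it. It bites if adherence is counted over the full 14 days and if some patients stop drug by the end of day 9 because they rebled.

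The size cannot be computed from the documents. Under the assumed equal shares, the per-protocol risk difference falls from 22.2 points to 18.5 at 25% removal (power 73%) or to 13.8 at 50% (power 56%). The risk ratio moves only from 0.29 to 0.26 at 50%, and the odds ratio does not move. A true effect could thus look non-robust because events are missing. The article sets no significance requirement for the per-protocol result, so this is a matter of interpreting a supporting analysis. It is worth correcting, but it does not threaten the primary conclusion.

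**What to change.** Add one sentence to the protocol or the analysis plan. For the per-protocol set, adherence is capsules taken divided by capsules scheduled up to the earliest of first rebleeding, protocol-directed discontinuation or day 14, and no participant is excluded for adherence or treatment changes on or after the first rebleeding. This governs the analysis set only and changes nothing in how patients are treated.

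The rule removes this outcome-dependent exclusion whichever denominator was intended. Patients who were poorly adherent before any rebleed are still excluded. The dated medication diary and the drug-return counts already supply the data. The article reports 48 participants enrolled of a planned 120 as of June 2026 and says that the analysis plan will be finalized before database lock and unblinding. The change can therefore be made blinded, at the cost of a wording amendment and a small change to the derivation of adherence.

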## Methods

### Study Design

In this double-blind, randomized controlled trial, patient allocation will be determined using a minimization-based dynamic randomization method. The stratification factors for allocation are as follows: (1) study site, (2) use of antithrombotic agents (yes/no), (3) history of CDB (yes/no), and (4) age at enrollment (≤69 y/≥70 y). Patients will be assigned in a 1:1 ratio to either the orengedokuto group (orengedokuto plus standard treatment) or the placebo group (placebo plus standard treatment).

The study setting parallels usual practice. Patients will be recruited from the gastroenterology inpatient departments of hospitals in different districts of Japan. A SPIRIT (Standard Protocol Items: Recommendations for Interventional Trials) 2025 checklist is provided in Checklist 1. A flowchart of the study is shown in Figure 1.

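### The fixed primary test, an unstratified Fisher exact test, is valid but conservative; a level-controlling alternative would gain a few points of power at the same sample size

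*Protocol article*

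**What the plan says.** Statistical Methods names the test for rebleeding in the full analysis set: "intergroup comparisons will be performed using Fisher exact test, consistent with the method used for sample size calculation". On the level it adds: "A 2-sided significance level of 5% will be applied". The one sensitivity analysis named for the primary end point repeats the comparison in the per-protocol set.

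Sample Size uses the same test: "Using the Fisher exact test for a 2-sample comparison of proportions, with the PROC POWER procedure in the statistical analysis system". The inputs are "Assuming a rebleeding rate of 31.3% in the placebo group (standard treatment only) and 9.1% in the orengedokuto treatment group", with "a 2-sided significance level of 5% and a power of at least 80% was estimated". The result is "the required sample size was calculated to be 57 patients per group", and "the planned total enrollment is set at 120 patients".

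Study Design describes 1:1 allocation by minimisation: "The stratification factors for allocation are as follows: (1) study site, (2) use of antithrombotic agents (yes/no), (3) history of CDB (yes/no"), with age group (≤69/≥70) as the fourth factor. None of the four enters the primary test. Further analysis details are left to a SAP that is not shown, but the primary test itself is fixed in the protocol.

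**The concern.** Fisher's test conditions on the total number of events. With few events it can reach only a few p-values near 5%, so its true error rate falls below the nominal level. At the planned rates the trial expects about 57 × (0.313 + 0.091) = 23 events, where this effect is not negligible. Consistency with the sizing method explains where the test came from, but it is not a reason to prefer it to another test that also holds 5%.

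A second, smaller issue is that balancing on prognostic factors and then leaving them out makes an unadjusted test more conservative still.

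What is at stake is some avoidable risk of missing a real effect. The Discussion concedes that the assumed effect rests on 11 treated patients and may be too large, so spare power has value here.

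**Working it through.** **Inputs.** Sample Size: placebo rate 0.313, orengedokuto rate 0.091, two-sided 5%, power at least 80%, n = 57 per group, 120 in total (60 per group if balanced).

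**Formulas.** Let p_F(x, y) be the two-sided Fisher p-value for x and y events.
- Power = Σ_x Σ_y Bin(x; n, 0.313) · Bin(y; n, 0.091) · 1{p_F(x, y) ≤ 0.05}.
- Size at a common rate p: the same sum with both rates equal to p.
- Boschloo: reject if p_F ≤ c, where c is the largest cut-off whose size, maximised over p, is at most 5%. This gives c = 0.0739 at n = 57 and c = 0.0665 at n = 60.

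**Step 1: the plan's own figure.** Fisher power is 79.3% at n = 56 and 80.3% at n = 57. The stated 57 per group is reproduced.

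**Step 2: true size of Fisher's test, equal groups.**

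| Common rate | n = 57 | n = 60 |
|---|---|---|
| 9.1% | 1.9% | 2.0% |
| 20.2% (mean of the two rates) | 2.85% | 2.8% |
| 31.3% | 3.2% | 3.1% |
| Maximum over all rates | 3.2% | 3.5% |

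Boschloo's maximum size is 4.9% at both sample sizes.

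**Step 3: power, equal groups, placebo rate 31.3%.** The 12% and 15% treated rates are assumptions, to show a smaller effect.

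| Treated rate | n | Fisher | Boschloo | Gain (points) |
|---|---|---|---|---|
| 9.1% | 57 | 80.3% | 85.4% | 5.1 |
| 9.1% | 60 | 82.6% | 85.9% | 3.4 |
| 12% | 57 | 64.3% | 70.7% | 6.5 |
| 12% | 60 | 66.4% | 71.4% | 5.0 |
| 15% | 57 | 46.5% | 53.1% | 6.6 |
| 15% | 60 | 48.0% | 53.6% | 5.6 |

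Gains are taken before rounding. Boschloo first reaches 80% power at about 51 per group, 57 − 51 = 6 fewer per group than Fisher. As an example at 57 per group, 15 against 6 events gives Fisher p = 0.051 and 12 against 4 gives p = 0.057. Both miss under the plan, and both are below Boschloo's cut-off of 0.0739.

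**Step 4: slightly unequal groups.** Fisher is at its most discrete when the groups are exactly equal. The same enumeration at 56 and 58 gives Fisher size of 2.8% to 4.1% over the three rates in Step 2. Power at the assumed rates is 84.8% (Fisher) against 86.5% (Boschloo) if placebo has the 56, and 82.4% against 84.7% if placebo has the 58. The gain is then about 2 points.

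**Step 5: how much is due to the factors?** The protocol gives no prevalences or effects, so all of these inputs are assumed: 114 patients, six sites, a biased coin of 0.8, three binary factors at 40% prevalence with a common odds ratio (OR), and 4,000 runs (Monte Carlo SE about 0.6 points at 85% power). Power at 31.3% against 9.1%:

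| OR per factor | Fisher | Unadjusted chi-square | Adjusted logistic score test | Chi-square − Fisher | Adjusted − chi-square |
|---|---|---|---|---|---|
| 1 | 81.9% | 86.3% | 86.7% | 4.4 | 0.4 |
| 1.5 | 81.3% | 85.5% | 86.3% | 4.2 | 0.8 |
| 2 | 82.7% | 87.9% | 89.8% | 5.3 | 1.9 |
| 3 | 82.7% | 87.4% | 90.7% | 4.7 | 3.3 |

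Most of the gap appears on leaving Fisher, before any factor is used. A separate simulation under minimisation (8,000 runs, log odds ratios 0, 0.5 and 1.0) gave chi-square 86.8%, 87.8% and 87.8%, against 85.0%, 86.4% and 88.0% for a stratified Cochran-Mantel-Haenszel (CMH) test, so stratifying brought no material gain there.

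In the first simulation, Fisher's size fell from 4.0% at OR 1 to 2.1% at OR 3 with a null rate of 31.3%. The adjusted score test's size ranged from 4.8% to 5.9%.

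**The case against.** The case for leaving the test alone is a fair one. Fisher's test holds 5%, the trial is sized and analysed with the same test, and the power target is met. Its conservatism has already been paid for in N, so no planned power is lost. The trial calls itself exploratory and expects a larger confirmatory study. By June 2026, 48 patients had been enrolled, and a change needs committee approval. All of this stands, and it limits the point to efficiency.

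A reader might infer more than the documents support:
- **That the trial is underpowered or the test invalid.** Step 1 shows otherwise.
- **That ignoring the minimisation factors is the main cause.** Step 5 attributes most of the loss to discreteness. Study Design lists the factors without a rationale and does not say that they are prognostic for rebleeding.
- **That no adjusted estimate will be produced.** The SAP is not shown and may contain one.
- **That Fisher's conservatism buys nothing.** This is true against Boschloo, which also guarantees the level. It is not true against the uncorrected chi-square test, whose size reaches 5.3% at 57 and 5.5% at 60 per group.

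What the objection does not answer is why Fisher should be preferred to a test with the same guarantee and more power, when the switch needs no further patients or data.

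**Conclusion.** The point holds as a modest, cheap improvement. At the assumed rates with equal groups, Fisher gives up 5.1 points of power to Boschloo at 57 per group and 3.4 at 60. The loss is about 5 to 7 points if the treated rate is 12% to 15% (assumed), and about 2 points at the assumed rates if the groups differ by two patients. The enumeration rests on the protocol's rates and on independent binomial outcomes. The further loss from unadjusted analysis ranges from nil to about 3 points in the simulations, and it depends on prognostic strengths that the protocol does not give.

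**What to change.** Amend the primary analysis before unblinding, with N unchanged, to one of the following:

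1. Boschloo's exact unconditional test at two-sided 5%. It answers the discreteness directly and guarantees the level under independent binomial outcomes.
2. An analysis adjusted for antithrombotic use, CDB history and age group: CMH, or a standardised logistic risk difference with 95% CI. The p-value would come from re-randomisation that replays the minimisation. Site belongs in a sensitivity analysis, because about 23 events cannot support that many cells.

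Keep the Fisher test as a sensitivity analysis in either case, and replace the appeal to the sizing method with a reason for the chosen test.

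The cost is a protocol amendment with committee approval and matching SAP text. No new data are needed, since the minimisation factors are entered at registration. The main technical risk lies in option 2 without re-randomisation: an asymptotic CMH or adjusted test can run slightly above 5% with so few events (up to 5.9% in the simulation).
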